## Abstract

**Background:**

Chronic insomnia is the most prevalent sleep disorder among military service members, and it compromises readiness, performance, and physical and mental health. Cognitive behavioral treatment for insomnia (CBTI) is the standard of care for the treatment of insomnia recommended by the VA/DoD Clinical Practice Guideline, the American Academy of Sleep Medicine, and the American College of Physicians. CBTI is highly effective but has limited scalability. It is often unavailable in clinical settings where service members receive sleep care. Digital technologies offer unique opportunities to scale and broaden the geographic reach of CBTI services and support increased patient access and engagement in behavioral sleep care. This study aims to evaluate the impact and acceptability of digital CBTI hubs to augment military treatment facilities’ capabilities in behavioral sleep medicine.

**Methods:**

This is a multi-site, non-inferiority randomized clinical trial designed to compare the effects of in-person (face-to-face or virtual) insomnia care as usual at three military sleep clinics versus CBTI delivered remotely and asynchronously through digital CBTI hubs. Digital CBTI hubs are led by licensed, certified clinicians who use NOCTEM’s® evidence-based clinical decision support platform COAST™ (Clinician Operated Assistive Sleep Technology). Changes in insomnia severity and daytime symptoms of depression and anxiety will be compared at baseline, at 6–8 weeks, and at 3-month follow-up. Patient satisfaction with insomnia care as usual versus digital CBTI hubs will also be examined. We hypothesize that digital CBTI hubs will be non-inferior to insomnia care as usual for improvements in insomnia and daytime symptoms as well as patient satisfaction with insomnia care.

**Discussion:**

Digital technology has a high potential to scale CBTI accessibility and delivery options required to meet the insomnia care needs of military service members. Digital CBTI hubs using COAST offer a novel approach to broaden service members’ access to CBTI and to serve as an augmentation strategy for existing sleep services at military treatment facilities. The pragmatic approach leveraging technology in this trial has the potential to rapidly inform clinical practice within the Defense Health Agency as well as other healthcare systems.

**Trial registration:**

ClinicalTrials.gov NCT05490550. Registered on 14 July 2023.

## Administrative information

Note: The numbers in curly brackets in this protocol refer to the SPIRIT checklist item numbers. The order of the items has been modified to group similar items (see http://www.equator-network.org/reporting-guidelines/spirit-2013-statement-defining-standard-protocol-items-for-clinical-trials/).

## Introduction

### Background and rationale {6a}

Chronic insomnia is pervasive among service members and degrades health and military readiness. Chronic insomnia is defined as difficulty falling or staying asleep that persists for at least 3 months and that results in one or more impairments in daytime functioning (e.g., memory and concentration difficulties; irritability; somatic symptoms; worry; absenteeism) [1]. Insomnia is the most common sleep disorder in military personnel, affecting approximately 20% of service members, with reported rates as high as 63% [2–5]. Marked increases in insomnia have been observed over the past two decades in service members in all branches of the US military, with military health surveillance data showing a 50-fold increase in the diagnosis of insomnia between 2005 and 2019 [6]. The consequences of insomnia on military effectiveness are well documented and result in increased healthcare utilization, lower rates of deployment, and higher rates of mental health disorders [7, 8]. Insomnia often occurs comorbidly with psychiatric and medical conditions including anxiety, depression, PTSD, TBI, suicidality, alcohol use disorder, hypertension, and diabetes and compromises performance, readiness, resilience, and safety [9–14]. Insomnia rarely remits on its own, and treatment is required for symptom improvement and remission [15, 16].

Cognitive behavioral treatment of insomnia (CBTI) is the first-line insomnia treatment. The VA/DoD, the American College of Physicians, and the American Academy of Sleep Medicine have all concluded that CBTI is the treatment of choice for chronic insomnia [1, 17, 18]. Non-pharmacological, behaviorally based treatments for insomnia are also generally preferred by patients [19–23]. For example, in a qualitative study of veterans with insomnia, 80% reported having negative prior experiences with sleep medications. In this same study, most veterans reported being receptive to behavioral insomnia treatment approaches, and all felt they could reasonably partake in CBTI sessions [23]. Despite the effectiveness of CBTI and patient preference for this approach, CBTI is underutilized and often not available in settings where service members receive healthcare.

Digital health technologies can help to overcome the limited scalability of in-person healthcare services, including CBTI. There are two primary barriers to the access and delivery of CBTI that digital health technologies target. First, digital health technologies broaden the geographic reach of services. Providers with specialty training in CBTI are not available across the military treatment facilities and clinics in the USA and abroad where service members receive care. Even if a service member is located at a treatment facility with a sleep clinic, clinical resources are focused on sleep-disordered breathing and other sleep disorders (e.g., hypersomnolence, parasomnias), restricting the availability of CBTI offerings [24]. Despite efforts to increase the number of providers trained in CBTI, geographic limitations remain [25, 26]. Furthermore, the extent to which providers outside of a specialty sleep clinic who are trained in CBTI consistently add a CBTI component to structured group or individual outpatient treatment programs is also uncertain [27]. Thus, developing and leveraging digital health tools to support the provision and implementation of reliable sleep assessments and delivery of CBTI in a wider range of clinical settings and by a broader group of providers could help to support the insomnia treatment needs of service members.

Second, digital health technologies create opportunities for increased patient access and engagement with healthcare services. The majority of service members own a smartphone and thus have familiarity with the use of the tools required for digital healthcare services [28, 29]. Traditional CBTI treatment sessions typically range from 5 weeks to several months. Digital health technologies alleviate patient burdens of attending weekly or bi-weekly in-person (i.e., face-to-face or virtual) sessions and minimize if not eliminate the need to account for travel time to and from the clinic and coordination with work, family, or childcare responsibilities [30–34]. For some service members, it may also alleviate the stigma associated with engagement in behavioral health care [35, 36]. Several studies have highlighted that guided interactions with a clinician during the use of digital health tools are key for patient engagement and optimal clinical outcomes [37, 38]. However, most currently available digital CBTI offerings, including web-based self-guided programs and self-help apps, do not support real-time and/or just-in-time provider-patient interactions and supervision. As service members are a high-risk occupation, those receiving CBTI require easy access to a provider who is able to address not only their clinical needs, but also address their ability to safely perform their military duties. To meet the needs of service members with chronic insomnia, a strategy that maximizes the current advantages of digital CBTI technology (i.e., increased reach and decreased patient burden) and that offers high-quality, clinician-supervised, military focused, and streamlined services with minimal added demands for clinicians and their patients is needed.

Our proposed strategy is the extension of CBTI services through digital CBTI hubs to augment the military sleep clinic’s capabilities. A digital CBTI hub consists of a trained licensed clinician who will use the Clinician Operated Assistive Sleep Technology (COAST™) platform developed by the digital behavioral sleep medicine company NOCTEM to deliver asynchronous, remote, and personalized CBTI to service members referred by military sleep healthcare providers. Briefly, COAST is a cloud-based software platform that consists of (1) clinician portal with embedded algorithms for the detection of sleep-disordered patterns, clinical decision support tools, and evidence-based materials for the management of insomnia; (2) cross-platform patient mobile app that includes daily self-report sleep/wake logs, adherence measures, and weekly assessments of symptoms, side effects, and progress; and (3) secure, two-way HIPAA-compliant text messaging to support patient engagement, adherence, and supervision.

Digital CBTI hubs may offer a unique strategy for scaling delivery and access to CBTI in four distinct ways. First, digital CBTI hubs can serve as an extension of clinical services offered by sleep, behavioral health, or primary care clinics and maintain the continuity of care between the healthcare providers and patients. Direct referral of patients with insomnia to a digital CBTI hub creates an opportunity for personalization of the CBTI delivery format and allows clinicians at military clinics to offer face-to-face services to more complex patients. Second, digital CBTI hubs have a broad geographical reach and can overcome the current transportation and distance challenges for service members throughout the world. Third, they provide patients with just-in-time access to a CBTI expert for supervision, guidance, and clinical and military duty-related counseling when and as needed. Lastly, with COAST, they overcome many of the barriers posed by conventional in-person CBTI such as wasted time in session for computing sleep diary metrics via paper sleep diaries.

Accordingly, the goal of this paper is to describe the design and analysis plan of the clinical trial to evaluate and compare the effectiveness of digital CBTI hubs using COAST as an augmentation strategy for the management of insomnia at three military sleep clinics relative to insomnia care as usual (ICAU). This clinical trial is the first to evaluate the extent to which digital CBTI hubs can support patient outcomes and the acceptability of this referral approach among service members with insomnia.

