Service members will be excluded from participation if they present with an untreated or under-treated comorbid sleep disorder that requires independent treatment or that may be exacerbated by CBTI interventions (e.g., obstructive sleep apnea, rapid eye movement (REM) sleep behavior disorder, or sleepwalking with a history of injury to self or others). Individuals will also be excluded if they are determined to be in acute psychiatric distress associated with marked impairments in functioning or that limits engagement in CBTI, adversely impacts the risk/benefit ratio of participating in the study, or requires immediate attention (e.g., attempted suicide in the past 6 months, seeking and/or receiving psychiatric treatment that requires inpatient or partial hospitalization level of care, requiring support of an assigned case manager for activities of daily living, active substance use disorder, past or current diagnosis or sub-threshold symptoms of psychotic or bipolar disorders, and untreated seizure disorder). Breastfeeding women or parents of an infant under the age of 3 months will also not be eligible, as their insomnia is confounded by these conditions, and CBTI may create greater-than-expected levels of transient sleepiness or fatigue. These minimal exclusion criteria are designed to support the recruitment of participants who are representative of adults with chronic insomnia and generalizable to real-life findings for military and civilian populations. The exclusion criteria that have been established are intended to minimize the risks associated with study participation. Nonetheless, each referring sleep medicine provider will use their clinical judgment to make determinations about the appropriateness of study participation, including CBTI for the patient, and will determine whether a patient is eligible for the study.

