#### Intervention description {11a}

Both intervention delivery formats, ICAU, and digital CBTI hubs using COAST will be delivered by credentialed masters or doctoral-level clinicians with experience in behavioral sleep medicine and include CBTI techniques. CBTI is a multi-component manualized cognitive-behavioral treatment protocol for the treatment of insomnia that is widely available. Among the various techniques that can be combined into CBTI, the most effective techniques to reduce insomnia are stimulus control and sleep restriction [40, 41]. Stimulus control aims to limit the use of the sleep environment (bed, bedroom) to sleep and directly addresses behaviors that disrupt circadian sleep–wake regulation mechanisms [42–44]. Sleep restriction involves the implementation of a regular sleep–wake schedule, which limits the time spent in bed while awake [45]. Relaxation techniques (e.g., progressive muscle relaxation, deep breathing, guided imagery) may also be helpful to reduce cognitive or physical hyperarousal that delays sleep onset [17].

Specifically, ICAU will include the usual care for service members diagnosed with insomnia at their local military treatment facility, as per the site’s current clinical practices. Treatment sessions will be conducted with the treating clinician(s) who typically receive insomnia referrals. Across sites, treatment duration will range from approximately 6 to 12 weeks with appointments scheduled every 1 to 3 weeks. Sleep metrics and progress will be evaluated and assessed by sleep diary, validated measures such as the Insomnia Severity Index and Epworth Sleepiness Scale, and patient self-report during scheduled sessions. All sessions will be conducted synchronously and in person (face-to-face, virtually). Patients may be required to attend a single sleep hygiene group seminar where foundational healthy sleep habits and relaxation skills are reviewed.

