Treatment via a digital CBTI hub includes CBTI delivered remotely and asynchronously via NOCTEM’s proprietary software platform COAST (Clinician Operated Assistive Sleep Technology) with a NOCTEM research clinician. All research clinicians are fully credentialed, licensed healthcare professionals certified in the use of COAST by NOCTEM. COAST is an adaptive digital health system that includes a clinician portal for prospective monitoring of side effects, progress, and adherence and algorithm-generated recommendations for the implementation of CBTI techniques; a patient application (“app”) with embedded sleep educational materials and self-report daily sleep diary and weekly assessments; and a secure HIPAA-compliant two-way messaging system that allows patients and clinicians to communicate directly in case of questions. Treatment sessions will be conducted across 6–8 weeks, with asynchronous clinical interactions occurring throughout the 6–8-week period with at least one interaction per week. Minimally, each week, the research clinician will send personalized recommendations for behavioral changes to the participant via the app and instruct the participant to review specific sleep tactics (written or audio CBTI interventional materials) that provide instruction on how to implement and the background for the CBTI techniques. Dialog regarding these recommendations will primarily be conducted via the COAST messaging system; however, at any time during the intervention, the participant or the clinician may request a synchronous telephone or in-person appointment.

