### Oversight and monitoring

#### Composition of the coordinating center and trial steering committee {5d}

NOCTEM will be responsible for providing administrative, data management, and technical support to all three participating sites. Working closely with the three site coordinators, NOCTEM will hold weekly internal meetings to review study progress and communications received from the site investigators and site coordinators to promptly address any issue that may arise. With the oversight of site investigators, the site coordinators will be responsible for communicating and implementing any approved modifications to the study procedures and processes. While coordinators will be the primary points of contact for referral to the NOCTEM research clinician at the local digital CBTI hub, site investigators and research clinicians may communicate directly as needed to address participants’ needs or updates. NOCTEM will hold quarterly videoconference meetings with all COAST clinicians to review progress, address any questions that may arise, and communicate all relevant updates to the conduct of the study. Those members of the research team who are involved with the treatment of patients within the study will not review data that involve the comparison of outcomes (i.e., adverse effects, treatment response). The study is no greater than minimal risk, and therefore, an independent research medical monitor is not required.

While stakeholders and the public will not officially be involved in the operations of this trial, through, for example, a Stakeholder and Public Involvement Group (SPIG), efforts to engage and collect feedback from these entities will be ongoing. Opinions of military sleep medicine physicians were sought prior to finalizing the study procedures, and we will aim to keep appraised Defense Health Agency stakeholders and leadership of study developments, progress, and outcomes through channels outlined in our dissemination plan (see the “Dissemination plans {31a}” section). Comprehensibility of participant consent and information forms will be assessed at each patient encounter, and any issues or suggestions for improvements will be reviewed by the study team.

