#### Adverse event reporting and harms {22}

Should any adverse events occur in the study, the site investigator will be informed and report events immediately to the IRB. For service members, the anticipated risks are believed to be minimal. Participants will be updated if any new information is learned pertaining to unforeseen risks.

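### Weekly side-effect questioning is described for the hub arm only, so any between-arm comparison of adverse effects would be open to ascertainment bias

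*Protocol article*

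**What the plan says.** **Hub arm.** The Background {6a} describes the COAST patient app as containing "daily self-report sleep/wake logs, adherence measures, and weekly assessments of symptoms, side effects, and progress". The Intervention description {11a} adds "a clinician portal for prospective monitoring of side effects, progress, and adherence". Hub treatment lasts 6–8 weeks with at least one clinician interaction per week.

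**ICAU arm.** According to the Trial design {8}, ICAU is given by non-research clinicians and is deliberately not standardized. The Intervention description {11a} states that "treatment duration will range from approximately 6 to 12 weeks with appointments scheduled every 1 to 3 weeks". On monitoring it says: "Sleep metrics and progress will be evaluated and assessed by sleep diary, validated measures such as the Insomnia Severity Index and Epworth Sleepiness Scale", together with what patients report at sessions. Side effects are not named.

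**Both arms.** The Trial design {8} includes sleepiness among the baseline questionnaires. The Outcomes section {12} repeats the ISI, PHQ-2 and GAD-2 at 6–8 weeks and at 3-month follow-up, and gives two satisfaction instruments at 6–8 weeks. One of these, the ITAS, asks how severe side effects are expected to be, not which ones occurred. The adverse-event rule {22} reads: "Should any adverse events occur in the study, the site investigator will be informed and report events immediately to the IRB".

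**Comparison.** The oversight section {5d} says that team members who treat patients "will not review data that involve the comparison of outcomes (i.e., adverse effects, treatment response").

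**The concern.** If one arm is asked about side effects every week in a structured form and the other is not, the recorded counts differ even when the true rates are equal. The oversight section places adverse effects beside treatment response as outcomes that are compared, so a reader can expect such a comparison to be reported.

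It could go wrong in two ways. An apparent excess in the hub may be nothing but more frequent asking. Or a real excess may be dismissed as exactly that. The protocol itself names the relevant risk when it explains an exclusion: "CBTI may create greater-than-expected levels of transient sleepiness or fatigue". The participants are active-duty personnel whose occupation the Background calls high-risk, and the trial has neither a data monitoring committee nor an independent medical monitor to weigh an imbalance. No later analysis can recover side effects that were never asked about in one arm.

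**Working it through.** The article gives no side-effect rate, margin or power, so there is no figure of its own to reproduce. The check sets the passages side by side and then shows how large the effect could be under stated assumptions.

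**Step 1: what is collected in each arm, as described**

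| | Hub | ICAU |
|---|---|---|
| Structured side-effect questions | weekly, in the app | none named |
| Sleepiness during treatment | not named separately | Epworth, given as an example of local measures |
| Scheduled contact | at least weekly for 6–8 weeks | every 1 to 3 weeks for about 6 to 12 weeks |
| Adverse-event rule | report when one occurs | the same |
| Common follow-up measure of side effects experienced | none listed | none listed |

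**Step 2: opportunities to ask in the first 6–8 weeks**

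- Hub: 6 to 8 weekly assessments.
- ICAU with sessions every 3 weeks: 6/3 = 2 to 8/3 = 2.7.
- ICAU with weekly sessions: 6 to 8.

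The gap in contacts therefore runs from none to threefold (6/2 = 8/2.7 = 3).

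**Step 3: illustration of size (all rates assumed)**

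Take the same true rate *p* in both arms. The observed rate is *p* × capture probability, so the spurious ratio is simply the ratio of the two capture probabilities. With *p* = 20%, capture of 90% in the hub and the planned 94 per arm:

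- Hub: 0.20 × 0.90 = 18%, or 94 × 0.18 = 16.9 cases.
- ICAU at 60% capture: 12%, 11.3 cases, ratio 1.5.
- ICAU at 45% capture: 9%, 8.5 cases, ratio 2.
- ICAU at 30% capture: 6%, 5.6 cases, ratio 3.
- ICAU at 90% capture: 18%, ratio 1, no distortion.

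The chance that a two-sided 5% test would show a significant hub excess, with *d* the difference in observed rates and p̄ their mean, is approximately

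Φ{[*d* − 1.96·√(2p̄(1−p̄)/94)] / √[(p₁(1−p₁) + p₂(1−p₂))/94]}.

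For 18% against 12%: (0.06 − 1.96 × 0.0521)/0.0519 = −0.81, which gives 21%. The other cases follow in the same way:

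| True rate | ICAU capture 60% | 45% | 30% |
|---|---|---|---|
| 10% | 12% | 23% | 41% |
| 20% | 21% | 44% | 72% |
| 40% | 43% | 80% | 98% |

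The article plans no such test. The table shows only how easily unequal capture could look like a finding.

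**The case against.** The strongest reply is that no tolerability comparison is actually planned. The objectives, outcomes and statistical methods contain no adverse-effect aim, endpoint, margin or test. The only mention is a sentence restricting who may see comparative data. That stands, and it limits the point: the conclusions on insomnia, depression, anxiety and satisfaction are untouched.

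A reader might infer that ICAU has no enquiry about harms at all, so that side effects are elicited in one arm and merely volunteered in the other. The text does not support that. It names the Epworth scale and session self-report for ICAU, and sleepiness is the very harm the protocol singles out. What remains is that the Epworth is offered as an example of non-standardized local practice and is not a listed study outcome at follow-up.

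A reader might also infer that no common measure exists. That cannot be asserted. The article is condensed, the schedule figure is not shown, and the data collection section {18a} does not confine the app to the hub arm. Nor, however, does it say that ICAU participants receive the weekly side-effect items.

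The weekly COAST items are described as clinical monitoring and are nowhere designated as trial harms data. That is fair, but nothing says they are kept out of a comparison either. Finally, the article presents the hub as augmenting usual care, so the point should not be argued as though replacement were claimed.

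**Conclusion.** The concern holds in a limited form. As described, side-effect ascertainment is structured and weekly in the hub and unspecified in ICAU. The shared adverse-event rule is passive, and a comparison of adverse effects is mentioned. A comparison drawing on those data would be open to ascertainment bias, most likely against the hub.

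The size is unknown. It is zero if capture is equal. It reaches a ratio of 1.5 to 3 under the assumed capture rates, which come from no source in the document and determine the ratio entirely. The direction rests on the assumption that more frequent structured asking captures more.

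The stronger conclusion, that the trial cannot show whether the hub is as well tolerated, goes too far: the trial sets no such objective, and events reported under the common rule could still be tabulated. This is an inexpensive improvement to harms data and not a threat to the planned efficacy or satisfaction results.

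**What to change.** - Give both arms the sleepiness scale already used at baseline and one short side-effect checklist at the existing 6–8-week and 3-month electronic assessments. The COAST side-effect items could serve as the checklist. It should ask about the whole period since the previous assessment, because the sleepiness of concern is transient.
- State that any between-arm comparison of adverse effects rests only on these commonly collected data, and that the weekly COAST items are kept for clinical use in the hub.
- If both arms already receive common items, say so and restrict the comparison to them.

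The cost is a few more questions at two assessments already scheduled, slightly more participant burden, and an amendment. One limit remains: ICAU can run to about 12 weeks, so some ICAU participants will still be in treatment at the 6–8-week assessment. The comparison should be read with that in mind.
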